### Attention Control Comparison Group

The standard comparison arm in parallel conventional exercise trials has historically been usual care. Currently underway is the HF-ACTION trial, a large multi-site NIH-funded study comparing usual care plus a conventional exercise program to usual care alone.Although we felt this design was reasonable for our pilot investigations, we recognize its inherent limitations. One important criticism for a usual care comparison group is that it does not properly control for the group social interaction that is present in our class-based intervention. We will address this issue in this proposal with a time-matched attention control.

Patients in the control group will attend education/social group sessions twice weekly. Classes will be structured as shown in Table 2. The first fifteen minutes of education will be led by the study nurse and follow the content of a series of pamphlets designed by the Heart Failure Society of America (HFSA) (we will purchase from [www.hfsa.org](http://www.hfsa.org/)). Additional information about blood cholesterol will be used from the National Heart, Lung and Blood Institute (NHLBI). These “Education Modules” are self-contained and written in easy-to-understand language. .

Module topics include:

1. Taking control of your heart failure
2. How to follow a low-sodium diet
3. Heart failure medicines
4. Self-care and dealing with HF symptoms
5. Exercise and activity
6. Managing feelings about heart failure
7. Tips for family and friends
8. Lifestyle changes
9. Advanced directives
10. Heart rhythm problems
11. New heart failure treatments
12. High blood cholesterol.

Topics will be distributed over the 12-week study period. Although more intensive educational interventions with HF nurses as part of a comprehensive multi-disciplinary management team have shown to be beneficial, there are actually few data on the effects of minimal education interventions in HF. While generally believed to be helpful, we do not expect these education pamphlets to have a major impact on our primary endpoints.

The remaining 45 minutes will consist of semi-structured group time moderated by the study nurse. Patients will be asked to discuss a given topic related to the HF module. We do not intend for this time to be used for medical consultation. The nurse will have explicit instructions to serve as moderator only and not to make any recommendations regarding an individual’s treatment. Throughout the 12-week program, the nurse will maintain a log to document class attendance

| Table 2. Details of Proposed Education Attention Control | | |
| --- | --- | --- |
| Week | Activities | Approximate Duration (min) |
| 1 | Introductory Session: Overview of Program  1. Description of class format  2. Description of Education Modules  3. Expectations of participants  Semi-structured Social Group | 5  5  5  45 |
| 2-12 | Presentation of HF Education Module content  Semi-structured Social Group | 15  45 |

As noted previously, patients in the intervention group will also receive the same 11 educational pamphlets, handed out weekly at Tai Chi class.

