## 2. STATISTICAL CONSIDERATIONS

### Sample Size Justification

We will enroll a total of 100 patients, with 50 patients in each group. We estimate that 75 of patients will be enrolled from BIDMC and 25 patients from other study sites (eg. BWH and MGH).

The sample size is based on power calculations using data from our pilot study. For these calculations, we assumed a 1) 10% loss of efficiency because we will use non-parametric tests and 2) 20% dropout rate. Although all patients enrolled in the pilot study completed that study, we did have a few missing data points. Therefore we felt it would be prudent to anticipate a larger dropout rate given prior experiences with HF patients.

Since there are three primary endpoints (change in six-minute walk, peak VO2, MLHF score), we will apply a Bonferroni adjustment to preserve the 5% level of significance. Based on pilot data, the standard deviation (SD) for change in walk test distance=317 feet; SD for change in peak VO2=2.1 ml/kg/min; and SD for change in MLHF score=17 points. Accounting for the above, the sample of 50 patients per group provides 80% power to detect a peak VO2 difference of 1.5 ml/kg/min between groups. We will have >90% power to detect a walk test difference of 240 ft and 83% power to detect MLHF score difference of 12.5 between groups, each of which is half the magnitude of difference observed in the pilot study. These differences represent clinically meaningful changes in functional capacity and quality of life.

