### Analysis Plan for Primary Specific Aims

To assess the adequacy of randomization, we will use Fisher’s Exact tests (categorical variables, e.g., sex, NYHA Class) and Wilcoxon rank-sum tests (continuous variables, e.g., age) to detect any differences in baseline characteristics between treatment groups.

Our three primary endpoints are change in exercise capacity and quality of life from baseline to 12 weeks using the six-minute walk, peak VO2 and MLHF score. Because we will recruit patients from 3 institutions, we will formally examine whether there is a site effect by performing Kruskall-Wallis tests to assess whether changes from baseline to 12 weeks differ by site for each outcome. In the event that we observe a site effect, we will proceed stratifying our analyses by site using van Elteren’s test. A priori, however, we do not expect to observe a site effect for a number of reasons, including the 3 institutions are academic tertiary care centers located in the same catchment area, they have similar patient profiles, and they apply the same standard of cardiac care by following ACC/AHA guideline. If no site effect is observed, we will proceed with our analyses by performing two-sample non-parametric Wilcoxon rank-sum tests to compare the distribution of change from baseline to 12 weeks between treatment and control groups for each outcome measure.

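### Both arms are treated in classes, but the power calculation and primary test make no allowance for within-class correlation, so the 5% familywise level and stated power are not assured

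*Protocol*

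**What the plan says.** Only the protocol is at hand.

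- **Randomization** is by individual patient, stratified by NYHA class (Procedures for obtaining Informed Consent).
- **Tai Chi arm:** one-hour classes twice a week for three months, taught by two instructors at several facilities and times of day (Intervention).
- **Control arm:** group sessions twice a week. After 15 minutes of education, "The remaining 45 minutes will consist of semi-structured group time moderated by the study nurse" (Attention Control Comparison Group). That section explains why usual care was not chosen as comparator: "it does not properly control for the group social interaction that is present in our class-based intervention".
- **Sample size** (Sample Size Justification): "We will enroll a total of 100 patients, with 50 patients in each group". The stated allowances are a "10% loss of efficiency because we will use non-parametric tests", a "20% dropout rate", and multiplicity over three primary endpoints: "we will apply a Bonferroni adjustment to preserve the 5% level of significance". Class size, ICC and design effect do not appear.
- **Primary analysis** (Analysis Plan for Primary Specific Aims): "performing two-sample non-parametric Wilcoxon rank-sum tests to compare the distribution of change from baseline to 12 weeks between treatment and control groups". The only alternative is van Elteren stratification by site, used if a preliminary Kruskal-Wallis test shows a site effect.

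**The concern.** Patients in one class share an instructor or nurse, a room, a time slot and each other's company for 12 weeks. If that shared exposure affects outcome, changes within a class are positively correlated. Each class lies wholly in one arm, so differences between classes add to the difference between arms. The null variance of a rank-sum test assumes independent observations and would then be too small.

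The per-test error would exceed 0.05/3, and Bonferroni would not deliver the 5% level for which the protocol adopts it. Power would also be lower than stated. The self-reported MLHF score is the endpoint where this is most plausible.

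This is more than detail left to a statistical analysis plan. The protocol names the primary test, lists its sample-size allowances and provides for one grouping factor. Class is not that factor: site means recruiting institution, and classes are held at a wider set of facilities and times.

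**Working it through.** **Inputs from Sample Size Justification.** 50 per arm; 20% dropout; 10% efficiency loss; familywise 5% over three endpoints, so 0.05/3 = 0.0167 per test (two-sided assumed, z = 2.394). For the walk test, "the standard deviation (SD) for change in walk test distance=317 feet" with a difference of 240 ft; peak VO2 SD 2.1 and difference 1.5; MLHF SD 17 and difference 12.5.

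**Step 1: the plan's own figures, with independent patients.** Effective n per arm = 50 × 0.8 × 0.9 = 36. Power = Φ(δ/SD × √(n/2) − z).

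- Peak VO2: 0.714 × 4.243 − 2.394 = 0.636, power 73.8% (stated 80%)
- Walk: 0.757 × 4.243 − 2.394 = 0.818, power 79.3% (stated above 90%)
- MLHF: 0.735 × 4.243 − 2.394 = 0.726, power 76.6% (stated 83%)

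With dropout only (40 per arm) the results are 78.8%, 83.9% and 81.4%. Peak VO2 and MLHF are then within 2 points of the stated values without any clustering term, so no clustering allowance is hidden in them. The shortfall from 80% to 74% is a separate matter. Only the further drop below 74% belongs to this point.

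**Step 2: assumptions the protocol does not supply.** Class size m from 4 to 10, ICC from 0 to 0.05, each patient in one class throughout.

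**Step 3: formulas.**

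- Design effect DE = 1 + (m − 1) × ICC
- Per-test error a = 2(1 − Φ(2.394/√DE))
- Familywise error, all three endpoints clustered = 1 − (1 − a)³
- Familywise error, MLHF alone clustered = 1 − (1 − 0.0167)²(1 − a)
- Power from n = 36/DE

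Example with m = 10, ICC 0.05:

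- DE = 1 + 9 × 0.05 = 1.45, and √1.45 = 1.204
- a = 2(1 − Φ(1.988)) = 0.0468
- Familywise error = 1 − 0.9532³ = 13.4%; MLHF alone = 1 − 0.9833² × 0.9532 = 7.8%
- n = 36/1.45 = 24.8, so peak VO2 power = Φ(2.517 − 2.394) = 54.9%

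| m | ICC | DE | Per-test error | Familywise, all three | Simulated | Familywise, MLHF only | Peak VO2 power |
|---|---|---|---|---|---|---|---|
| any | 0 | 1.00 | 1.67% | 4.9% | 4.5-4.8% | 4.9% | 73.8% |
| 4 | 0.01 | 1.03 | 1.83% | 5.4% | not run | 5.1% | 72.3% |
| 5 | 0.01 | 1.04 | 1.89% | 5.6% | not run | 5.1% | 71.8% |
| 4 | 0.02 | 1.06 | 2.01% | 5.9% | not run | 5.2% | 70.9% |
| 5 | 0.02 | 1.08 | 2.12% | 6.2% | not run | 5.4% | 69.9% |
| 4 | 0.05 | 1.15 | 2.56% | 7.5% | not run | 5.8% | 66.7% |
| 10 | 0.02 | 1.18 | 2.75% | 8.0% | 7.0-7.4% | 6.0% | 65.4% |
| 5 | 0.05 | 1.20 | 2.89% | 8.4% | 7.7-8.0% | 6.1% | 64.5% |
| 8 | 0.05 | 1.35 | 3.94% | 11.3% | 10.8-10.9% | 7.1% | 58.5% |
| 10 | 0.05 | 1.45 | 4.68% | 13.4% | 12.2-12.6% | 7.8% | 54.9% |

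The simulations ran three rank-sum tests with 40 completers per arm, 10,000 runs per setting, and between-endpoint correlation 0 or 0.3. They fall slightly below the formula and lead to the same conclusion.

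**The case against.** A reader might infer that the standard errors are too small and that the 5% level is not held. The documents do not support that as fact. Both need an ICC above 0 and a class size, and the protocol gives neither; at ICC 0 nothing is lost.

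Classes may well be small. The Data Safety and Monitoring Board section describes a three-year period of Tai Chi sessions. With even enrolment, 50 × 12/156 gives about 3.8 Tai Chi patients in class at any time, over all locations. Batched cohorts would be larger, but classes of 8 to 10 are an upper case. Patients may also move between class times, which would dilute the correlation. Instructor training, video review and the nurse's limited role as moderator should reduce differences between classes.

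Peak VO2 is measured by blinded technicians, so applying the MLHF's ICC to it is pessimistic. That is why the table has an MLHF-only column.

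A reader might also take the sentence about group social interaction as naming an active ingredient, or as conceding correlation. It does neither. It criticises a usual-care comparator, and the answer given is a control arm matched for contact time. That balances the average effect of group contact between arms but leaves correlation within classes untouched. Nor can confidence intervals be called too narrow, since the protocol states none for the primary endpoints.

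These arguments limit the size. They do not supply the missing allowance. Site stratification is only a partial answer: it is conditional on a preliminary test and does not address class.

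**Conclusion.** The point holds in conditional form. Delivery is in groups in both arms, while the stated power and the fixed primary test treat patients as independent. Whether this matters depends on class size, ICC and stability of class membership, all unstated.

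The effect is negligible at ICC 0 and small with 4 to 5 per class at ICC 0.01 to 0.02 (familywise error about 5.4% to 6.2%). It becomes material at ICC 0.05 or with classes near 10. The upper end, about 12-13%, needs 10 per class and ICC 0.05 on all three endpoints. With clustering of the MLHF score alone, the ceiling in this range is about 8%. The loss of peak VO2 power runs from 1 or 2 points to about 19.

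The direction is certain for any positive ICC; the size is not. Given the protocol's stated aim of preserving the 5% level, the change is worth making.

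**What to change.** 1. Record the class or group each patient attends, in both arms, and any change of class. The attendance logs are the natural place, but the protocol does not say that they identify the class.
2. Prespecify a primary analysis that respects class: a clustered rank-sum test, which keeps the non-parametric approach, or a mixed model with a class random effect and small-sample degrees of freedom. At minimum, make this a prespecified sensitivity analysis beside the planned test.
3. In Sample Size Justification, state the assumed class size, ICC and design effect, and restate power for all three endpoints.

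The data and wording cost little. The real costs are somewhat wider uncertainty, lower stated power, and a class variance estimated from few classes: with 40 completers per arm, about 10 classes of 4 or only 4 classes of 10. Holding the precision of 100 independent patients by enrolment would take 100 × DE: 104 patients at 5 per class and ICC 0.01, 120 at 5 and 0.05, and 146 (145 rounded up to equal arms) at 10 and 0.05. If enrolment stays at 100, the lower power should be stated.

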### Measurement Protocols

Patients will be tested at three time points: baseline, 6 weeks, and 12 weeks. Patient interview, questionnaires, blood tests, and six-minute walk will be conducted at all three time points. Cardiac tests (bicycle metabolic stress test) will be done only at baseline and 12 weeks. Tests will be coordinated to maximize patients’ convenience. BIDMC and BWH are within close walking distance on the Longwood Medical Campus. Taxi vouchers will be available should patients require the short cab ride. A free shuttle bus is available every 15 minutes between the BWH and MGH. As mentioned previously, we will conduct a brief follow-up phone call at 6 months to assess current health status, quality of life using the Minnesota Living with Heart Failure Questionnaire, use of healthcare (numbers of hospitalizations and emergency department visits since the 12-week interview), and practice of Tai Chi and other exercise.

**Exercise Capacity and Functional Status**

### Six Minute Walk Test

The six minute walk test is a standardized assessment that measures the distance walked in meters down a corridor at a comfortable pace. The test will be done early in the visit on each of three occasions, at least 2 hours before the bicycle ergometer test. Patients will be read standardized, scripted instructions by a research assistant who is blinded to treatment arm. The assessor will stand in silence at one end of the straight, uncluttered corridor and will inform the patient when there are 3 minutes and 1 minute before the end of the test. Patients will be allowed to stop as often as they need if they fatigue. The six-minute walk test has been shown to be an independent predictor of HF prognosis and survival in pharmacologic trials.

### Timed Get-Up and Go Test

We will conduct the timed “Timed Get-Up and-Go", which is a reliable and valid test for quantifying functional mobility that may also be useful in following clinical change over time. The "timed get up and go test" requires patients to stand up from a chair, walk a short distance (3 meters, ~10 feet) at a comfortable pace, turn around, return, and sit down again. This test will be timed by the blinded research assistant. The patient will repeat the test and the times will be averaged. The test is quick, requires no special equipment or training, and is easily included as part of the routine medical examination. The timed score has been shown to be reliable and to correlate well with log-transformed scores on the Berg Balance Scale (r = -0.81), gait speed (r = -0.61) and Barthel Index of ADL (r = -0.78). The “timed get up and go test” will be performed at baseline, 6-weeks and 12-weeks.

### Peak Oxygen Uptake on Bicycle Metabolic Stress Test

Bicycle metabolic stress tests will be performed either at the Cardiac Testing Center at Brigham and Women’s Hospital or at Beth Israel Deaconess Medical Center and will be paid for by NIH grant award R01 AT002454. Technicians and physicians performing tests will be blinded to study group. Patients will perform a symptom-limited exercise test using a bicycle ramp protocol to determine peak VO2. Testing will be done on an electronically calibrated upright bicycle, with expired gas analysis under continuous electrocardiographic monitoring. Blood pressure will be taken at 3-minute intervals and just prior to stopping exercise. Participants will be encouraged to exercise to exhaustion. Perceived exertion will be measured using the 1-10 Borg Scale. Respiratory gas analysis will be performed on a breath-by-breath basis using a Sensormedic metabolic cart. Peak values will be averaged from the final 20 seconds of the test. Peak VO2 has been shown to correlate with cardiac output and skeletal muscle blood flow and has been an important criterion to assess when patients should undergo cardiac transplantation. Study investigators will send a copy of the test results to the attending physician with consent of the study subject.

## Quality of Life (QOL) and Psychosocial Functioning

*Patient interviews will be conducted at baseline, 6 weeks, and 12 weeks. All questionnaires will be administered by a research assistant who is blinded to the patient’s study group.* We will pilot test the survey instruments on 5 patients to determine participant burden.

To capture health-related QOL, we will use a disease-specific questionnaire, the Minnesota Living with Heart Failure (MLHF) Questionnaire and a generic Medical Outcomes Survey Short Form (SF-36) health status survey. Comparisons of these instruments in heart failure suggest that a more comprehensive assessment is gained by using multiple instruments. In addition, we will use the Profile of Mood States assessment (POMS) to more specifically capture mood and emotional status.

### Disease-Specific QOL Measure

The main QOL measure (and one of the primary endpoints that are accounted for in the power calculation) will be the disease-specific MLHF. This validated instrument is the most-commonly employed health status measure in HF. It consists of 21 items covering physical, psychological, and socioeconomic dimensions (e.g. swelling in the ankles, difficulty climbing stairs, fatigue, feeling depressed, spending money for HF). The score range is 0 to 105, with a lower number denoting better QOL. Prior studies have reported that a score of seven indicates some degree of impaired quality of life and that an improvement of five points represents a clinically significant change.

### Emotional Status/Mood

The POMS is a well-validated instrument for assessing emotional states that are transient and expected to respond to clinical intervention. It has been widely used to assess the effects of exercise interventions. The instrument consists of 65 single-word items rated on a 5-point scale to indicate recent mood in 6 dimensions: tension/anxiety, depression/dejection, anger/hostility, vigor/activity, fatigue/inertia, and confusion/bewilderment. A decreased total mood disturbance score denotes an improved emotional state. Test-reliability coefficients are reported to range from 0.65 to 0.74.80 Studies of Tai Chi have reported improvement in mood, decrease in anxiety, and enhancement in vigor as measured by the POMS scale.

### Self-Efficacy

The Cardiac Exercise Self-Efficacy Instrument (CESEI) is a validated 16-item scale that assesses patient’s confidence to perform certain physical exercises on a 5-point scale (no confidence to very confident). Score range is 16-80, with a higher number denoting increased self-efficacy. Stability and internal consistency estimates are about 0.9.

## Neurohormonal Status

*Blood tests will be conducted at baseline, 6 weeks, and 12 weeks for all patients. All blood tests will be obtained and analyzed by the BIDMC General Clinical Research Center. However, test results from the various blood tests will not be provided to the attending physician for two reasons. First, the General Clinical Research Center is not a CLIA certified lab and is not results are not allowed to be used for clinical purposes. In addition, blood tests are not run in “real time”; instead they will be run in batches at the end of the study period. Patients eligible for this study are typically a highly monitored patient population and these tests are not meant to substitute for routine medical care.*

BNP samples will be analyzed on whole blood collected in EDTA using a commercially available Biosite Triage BNP Test point-of-service meter (fluorescence immunoassay). Serum BNP >100 pg/ml supports a diagnosis of symptomatic heart failure. TNF- and c-reactive protein will be determined using commercial ELISA kits.

## Autonomic Tone

### Catecholamines

Plasma norepinephrine, epinephrine,and dopamine will be measured by high performance liquid chromotography/electrochemical detector. Resting catecholamine samples will be drawn on ice in heparinized tubes after 20 minutes of lying quiet in a supine position with intravenous catheter in place. Analyses for norepinephrine, epinephrine, and dopamine will be performed using high-performance liquid chromatography/electrochemical detector. Norepinephrine level has been identified as one of the strongest predictors of HF progression, functional status, and death. In the Studies of Left Ventricular Dysfunction(SOLVD), norepinephrine levels above the median value were twice as likely to be associated with death from HF.33

## Medical Utilization and Collection of Cost Data

Medical record, interview data, and automated utilization data will be used to document patients’ use of health care during the study period. We will collect information on visits to healthcare providers, telephone contact with health care providers, use of prescription and over the counter medications, use of radiology and laboratory tests, hospitalizations, and other invasive or non-invasive cardiac procedures (e.g., cardiac catheterizations, cardioversion, pacemaker implantation). We will track both insurance payments and out-of-pocket expenses.

We will compare the health care resources used by patients randomized to education attention control to resources use by patients randomized to Tai Chi. Information will be obtained through patient self-report. Studies that have primarily relied on patient interview have found that the average error in self-reported utilization is small.97 However, for those patients referred from the BIDMC, we will also utilize the hospital database and online medical record system that tracks office visits, telephone contacts, hospitalizations, emergency room visits, radiology and laboratory tests, procedures, and prescription medications. This will allow us to check self-reported utilization by comparing self-report data with that captured through the hospital database. We will not track these electronic data at any other site since database systems of those hospitals are not fully integrated online, and thus, would not yield comparable information.97 A standardized Medicare Fee Schedule will be used to assign an estimate of costs in dollars to hospitalizations and visits to physicians and nurses. The fee schedule also will assign cost estimates to prescription medications, lab and radiology tests, and cardiac procedures. Costs of over the counter medications will be estimated based on wholesale costs and average national dispensing costs.

